### Data Collection

Data collection occurred continuously during each patient’s hospital stay, including assessments at admission and discharge to document patient demographics, comorbidities, pharmacotherapy details, and DRPs. These data will help evaluate the prevalence and types of DRPs, intervention acceptance rates, and changes in patient understanding of pharmacotherapy.

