**Methods:**

This prospective, uncontrolled study was conducted over 1 year in the Vascular Surgery Department at the National Institute of Cardiovascular Diseases in Bratislava, Slovakia. The study included adult patients with carotid artery disease or lower extremity artery disease who were on 3 or more medications, with an estimated sample size of approximately 100 patients. The primary intervention involved 3 key changes in practice: medication reconciliation at both admission and discharge, where hospital pharmacists review and verify medication lists; medication review to identify and address drug-related problems; and patient education at discharge. Pharmacist-proposed interventions were documented and communicated to the physician for treatment adjustments. The primary outcome is the change in drug-related problem prevalence from hospital admission to discharge. Secondary outcomes include the acceptance rate of pharmacist recommendations and patient understanding of pharmacotherapy. Data collection involved documenting the number, type, and frequency of drug-related problems; the anatomical therapeutic chemical classification of medications associated with drug-related problems; and patients’ social, demographic, and clinical characteristics, with a focus on factors related to drug-related problems, comorbidities, and medication use. Data analysis will use the paired Wilcoxon signed-rank test to compare the prevalence of drug-related problems and medication counts between admission and discharge. Continuous variables will be presented as means (SDs), while categorical variables will be reported as counts and percentages. Patient understanding of pharmacotherapy will be evaluated using a 3-point scale, classifying understanding as good (2-3 points per medication), modest (1-2 points), or poor (0-1 point).

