### Variables

The variables collected include the number, type, and frequency of DRPs; ATC of drugs causing DRPs; medical, social, and demographic characteristics of patients; health condition of patients; comorbidities; and patient understanding of their pharmacotherapy assessed on a 3-point scale at hospital admission.

We assessed the patients’ basic social, demographic, and clinical characteristics, with a particular emphasis on evaluating their pharmacotherapy and the incidence of DRPs. Additionally, we examined the degree of acceptance of pharmacists’ recommendations by physicians and the outcomes of DRP resolutions. Our analysis will also identify the medications most frequently associated with the occurrence of DRPs. Patients’ understanding of their pharmacotherapy was also be evaluated.

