One of the recorded parameters is patient understanding. This is evaluated in 3 steps and scored as 0 or 1: The patient knows (1) or does not know (0) the name of the drug, the patient knows (1) or does not know (0) the indication of the drug, and the patient knows (1) or does not know (0) the dosage of the drug. The 3-point scale was based on previously published studies by Cline et al [52], Boonstra et al [53], and Marfo et al [54], who evaluated patients’ knowledge based on their understanding of the drug name, dosage, duration of treatment, indication, relationship of the drug to food, duration of therapy, or route of administration. If the patient was unable to attend the interview, other sources were used to obtain a medical history or to clarify conflicting information. Other resources should never be a substitute for a thorough conversation with the patient or family members.

Regarding verification and documentation of the BPMH, the BPMH list should be verified by more than one other source. Sources for the initial acquisition of an overview of pharmacotherapy are the admission report, the history of hospitalization, outpatient reports, HIS, and the course at admission.

According to the World Health Organization standard operating procedure, a retroactive MedRec model was used for our biomedical research. In a retroactive model, in accordance with the aforementioned method, the patient is admitted by a physician in cooperation with a nurse by default, and a drug course—a daily prescription of drugs for the patient – is created. In this case, the BPMH is determined after admission by a physician or nurse.

The result of the MedRec is a comparison of medicines prescribed to and actually used by patients (BMPH) with marked discrepancies.

During the process of obtaining the BPMH, the pharmacist informs patients to always share their doubts about the correct use of the medication with the medical staff.

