##### MedRec by Pharmacists at Patient Discharge

The pharmacist performs MedRec when discharging a patient from the hospital, similar to the process at admission. When evaluating a patient’s pharmacotherapy on discharge from hospital, the BPMH obtained at the patient’s admission will be used as a source of information. The BPMH is then compared with the list of medicines that are recorded in the release report. The pharmacist will compare 2 lists of medicines, focusing on the identification of DRPs with special regard to the re-introduction of the chronic therapy the patient was taking before hospitalization. As part of this research, the pharmacist met with the patient during his or her discharge from the hospital and discussed with him or her the management of further pharmacotherapy. Pharmacists provided an understandable summary list of a patient’s medicines explaining the importance and the correct use of the medicine.

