### Statistical Methods

Continuous variables will be characterized as the mean with standard deviation. Categorical variables will be expressed as numbers and percentages.

To compare the number of drugs, active substances, and DRPs at hospital admission and discharge, the paired Wilcoxon signed-rank test will be used due to the non-normal distribution of differences between the 2 time points. Normality will be assessed with the Shapiro-Wilk test. To determine the effect size of the intervention, Cohen *d* will be calculated and categorized as small, medium, or large based on established intervals. Patients’ understanding of their pharmacotherapy at hospital admission will be evaluated using a 3-point scale. The average score per medication will be calculated, categorizing patients into groups based on their understanding: good (2-3 points per medication), modest (1-2 points per medication), and poor (0-1 point per medication).

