## Discussion

### Importance

The PHAROS study is the first prospective clinical trial in Slovakia to evaluate pharmacist-led interventions on DRPs in vascular surgery patients. Our findings add to the growing body of evidence that pharmacist involvement can reduce the prevalence of DRPs, improve patient understanding of medications, and enhance overall pharmacotherapy outcomes for hospitalized patients.

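### Patient understanding is described as scored only at admission, before the discharge education, yet the article promises to evaluate changes in it and credits its findings with supporting improvement

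*Protocol article*

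**What the plan says.** The Secondary Outcomes section names patient understanding of pharmacotherapy as one of two secondary outcomes, without a time point. The abstract does the same and adds the good, modest and poor categories.

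The time point appears in two other places. Variables lists "patient understanding of their pharmacotherapy assessed on a 3-point scale at hospital admission". Statistical Methods says that patients' "understanding of their pharmacotherapy at hospital admission will be evaluated using a 3-point scale". The scoring itself (one point each for knowing the drug's name, indication and dosage) is set out in the section on medication reconciliation at admission, which introduces it with "One of the recorded parameters is patient understanding".

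Education comes later. The abstract lists, as the last of the three practice changes, "and patient education at discharge". The section on reconciliation at discharge describes a meeting with the patient and adds: "Pharmacists provided an understandable summary list of a patient’s medicines explaining the importance and the correct use of the medicine".

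Two passages speak of change. Data Collection states: "These data will help evaluate the prevalence and types of DRPs, intervention acceptance rates, and changes in patient understanding of pharmacotherapy". Importance, in the Discussion, says that the study's findings add to the evidence that pharmacist involvement can, among other things, "improve patient understanding of medications".

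**The concern.** A change within patients needs a score before and a score after. The article describes only the earlier one, and it precedes the component most likely to alter understanding. A score of that kind is a baseline characteristic. It can describe how well patients knew their medicines on arrival and may help to identify those at risk of drug-related problems, but it carries no information on what the education achieved.

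The risk lies in reporting. Understanding is one of only two secondary outcomes, and the milestones section includes it in the full analysis and says that findings on the impact of the interventions were prepared for dissemination. The outcome statements give no time point, and two other passages speak of change and improvement. A pre-education score could therefore be presented as an effect of education.

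**Working it through.** The article gives no figure for this outcome, so there is nothing numerical to reproduce. The stated requirement of 94 patients belongs to the Wilcoxon signed-rank calculation and has no bearing here. The check is a comparison of the sections.

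1. **When is understanding scored?** Variables: at admission. Statistical Methods: at admission. Scoring procedure: within admission reconciliation. All three agree, and the first two name the time point explicitly.

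2. **When is education given?** Abstract: at discharge. The section on reconciliation at discharge: in the meeting held as the patient leaves. The only described score therefore comes first.

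3. **Is a second score described?** The three discharge sections mention comparison of medicine lists, identification of drug-related problems, discussion with the patient, an explained summary list and a completed discharge form. None mentions scoring understanding. The list in Data Collection of what is documented at admission and discharge (demographics, comorbidities, pharmacotherapy, drug-related problems) also leaves understanding out. That omission is weak evidence alone, because the list leaves out even the admission score.

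4. **Is a change analysed?** The paired Wilcoxon test in Statistical Methods is applied to the number of drugs, active substances and drug-related problems. For understanding, the plan is an average score per medication and three categories, with no comparison between time points.

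5. **What would a change require?** For patient *i*, change = score at discharge − score at admission. As described, only the second term exists. The quantity is undefined for every patient, so a larger sample would not help.

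6. **Could a control group replace the missing score?** No. Study Design calls the trial uncontrolled, and the limitations confirm that there was no control group.

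Steps 1 to 4 are consistent with one another: a single descriptive score at admission. The statements in Data Collection and Importance do not fit them.

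**The case against.** The strongest reply is that silence does not prove absence. The section on reconciliation at discharge opens with "The pharmacist performs MedRec when discharging a patient from the hospital, similar to the process at admission", and understanding is a recorded parameter of the admission process. The contents of the discharge form are not given, the procedure figure is not available in the text reviewed, and a journal article condenses a fuller protocol. A reader might infer that no second score exists and that there are no paired observations at all. The documents do not support so firm a statement; they support only that no discharge score is described. This part of the objection stands, and the remedy has to allow for both cases. It does not remove the conflict. If discharge scores do exist, the two sections that name admission alone are incomplete and the paired analysis is missing from the methods.

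A second reply is that the formal outcome is understanding, not change in understanding. The hypotheses concern drug-related problems only, and the Introduction treats low understanding as an indicator of risk, which fits a descriptive measure at admission. This also stands. A reader might infer that the secondary outcome fails at its declared purpose, but its definition never promised an effect. The fault lies in the passages that go beyond the definition.

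Third, the Importance sentence is a general Discussion statement, hedged with the word can, and neither conclusion section claims better understanding. That makes it weaker evidence than the Data Collection sentence. Its subject, however, is this study's own findings, so it credits the data with support they cannot give as described.

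**Conclusion.** The inconsistency holds. On the measurement and analysis described, neither a change in understanding nor an improvement after education can be estimated. This rests on reading the two explicit references to admission as complete; it would be revised if a discharge score was collected.

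The severity is moderate. One untested secondary measure is affected. The primary outcome, the hypotheses, the paired test and the sample size are not. Nor is scoring understanding at admission a mistake in itself, since it is a reasonable descriptive measure when labelled as such.

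**What to change.** The authors should first establish whether understanding was scored again at discharge.

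- **If it was not:** state the secondary outcome in the abstract and in Secondary Outcomes as understanding at admission, descriptive. In Data Collection, drop the reference to changes so that the sentence refers to understanding at admission. In Importance, take improved understanding out of what the findings are said to support. Recruitment has closed, so this costs wording and one claim.
- **If it was:** state the discharge score in Variables, in the section on reconciliation at discharge and in Statistical Methods, including whether it was taken after the education and which medicines it covered. Then analyse the paired admission-discharge change. This costs a few sentences and one further analysis of data already held. Because the trial is uncontrolled, the result should be reported as a before-after change and not as a proven effect of education.

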### Analysis and Reporting Milestones

For the initial data review, preliminary data analyses began in August 2023 to assess recruitment efficacy and data integrity. This phase includes an initial assessment of DRPs and intervention types recorded during patient admission.

The primary analysis, including full data analysis encompassing outcomes related to DRP reduction, intervention acceptance, and patient pharmacotherapy understanding, was completed in January 2024.

For the final report and dissemination, the study findings, including the impact of pharmacist interventions on patient outcomes, were compiled and prepared for dissemination by June 2024.

A timeline of the PHAROS trial (Figure 2) illustrates each phase of the study, from patient recruitment through final analysis and reporting.

These timeline indicators and progress markers will enable ongoing tracking of study completion and ensure that each stage of data collection and analysis aligns with the study’s objectives.

**Figure 2 figure2:**
[figure not shown]
Timeline of the PHAROS trial.

### Statistical Methods

Continuous variables will be characterized as the mean with standard deviation. Categorical variables will be expressed as numbers and percentages.

To compare the number of drugs, active substances, and DRPs at hospital admission and discharge, the paired Wilcoxon signed-rank test will be used due to the non-normal distribution of differences between the 2 time points. Normality will be assessed with the Shapiro-Wilk test. To determine the effect size of the intervention, Cohen *d* will be calculated and categorized as small, medium, or large based on established intervals. Patients’ understanding of their pharmacotherapy at hospital admission will be evaluated using a 3-point scale. The average score per medication will be calculated, categorizing patients into groups based on their understanding: good (2-3 points per medication), modest (1-2 points per medication), and poor (0-1 point per medication).

## Discussion

### Importance

The PHAROS study is the first prospective clinical trial in Slovakia to evaluate pharmacist-led interventions on DRPs in vascular surgery patients. Our findings add to the growing body of evidence that pharmacist involvement can reduce the prevalence of DRPs, improve patient understanding of medications, and enhance overall pharmacotherapy outcomes for hospitalized patients.

### Comparison With Prior Work

Several studies have examined the role of pharmacists in preventing and managing DRPs across various clinical settings [57], including vascular surgery. Hohn et al [45] and Martínez López et al [51] documented a decrease in DRPs due to pharmacist-led interventions, reporting an average of 1.3 and 1.7 DRPs per patient, respectively. These studies support the role of pharmacists in reducing DRPs and improving medication safety in hospitalized patients. Findings from Schmelzer et al [58] and other international studies also demonstrated a significant reduction in DRPs at discharge.

The impact of pharmacist-led interventions on vascular surgery patients specifically has not been extensively studied. However, studies in other settings, such as those by Hohn et al [45] and Rychlíčková et al [59], have shown positive outcomes from pharmacist interventions. Singh et al [60] highlighted the underprescription of statins in patients with peripheral artery disease, attributing this to clinician-related barriers such as concerns about adverse effects. The PHAROS study aims to contribute to this literature by demonstrating that pharmacist involvement in MedRec and MedRev supports DRP management and optimizes pharmacotherapy, underscoring the importance of pharmacist intervention in promoting guideline-adherent care.

An important aspect of the PHAROS study is its focus on patient education. Based on the prior literature, educating patients about their medications is strongly associated with better adherence and a reduction in DRPs [31,32,61,62]. Including patient education as part of the pharmacist’s role is intended to support informed patient participation in their treatment.

### Challenges and Barriers

Despite the promising outcomes of pharmacist-led interventions, challenges remain in their implementation. One significant barrier is resistance to change among health care professionals, especially in settings where the role of pharmacists in medication management is not well established. As noted by Hohn et al [45], physicians may be hesitant to accept pharmacist recommendations, particularly in complex cases involving polypharmacy and comorbidities. Successful pharmacist-led interventions require clear protocols, comprehensive training, and effective collaboration with other health care professionals. The lack of legislative requirements for MedRec and MedRev in Slovakia demonstrates the need for policy changes to integrate pharmacists systematically into patient care transitions. This is particularly important, as international guidelines, such as those from the European Association of Hospital Pharmacists [63], emphasize the role of MedRec in ensuring safe and effective care.

### Future Directions

Building on the results of this pilot study, future research should seek to validate these findings through a larger, randomized controlled trial, which would allow for a more rigorous assessment of pharmacist-led interventions on DRPs. Such studies could incorporate a control group, a larger sample size, and postdischarge follow-up to evaluate long-term effects. Expanding research to diverse health care settings and patient demographics could provide insights into optimizing pharmacist interventions across various clinical contexts.

### Limitations of the Study

Our study has several limitations. First, it was conducted as a single-center trial and performed in specific departments and with specific indications; therefore, the results may not be applicable under different conditions. Second, the study did not include a control group. Although all investigators were trained in all study processes, some degree of subjectivity is possible in the assessment of DRPs. Moreover, the number of patients was limited. However, trained hospital pharmacists strengthened the methodology used in our trial.

### Conclusions

The study should determine that pharmaceutical care provided at hospital admission and at hospital discharge could reduce the prevalence rates of DRPs in our study setting. The pharmacist-led interventions upon hospital admission and discharge, followed by patient education, might be implemented in daily practice in health care in our hospital.

## Abbreviations

ADR: adverse drug reaction
ATC: Anatomical Therapeutic Chemical Classification
BPMH: best possible medication history
DRP: drug-related problem
HIS: hospital information system
MedRec: medication reconciliation
MedRev: medication review
PCNE: Pharmaceutical Care Network Europe Association
SQUIRE: Standards for Quality Improvement Reporting Excellence
